## Introduction

Dual antiplatelet therapy (DAPT) including aspirin and a potent P2Y12 receptor inhibitor (prasugrel or ticagrelor) [1, 2] is the current standard of care in patients with non-ST-segment elevation acute coronary syndromes (NSTE-ACS) [3, 4]. In the absence of contraindication, aspirin is routinely administered to all patients as soon as the initial diagnosis is established, irrespective of subsequent management strategy [3]. Conversely, the risk/benefit ratio of the administration of potent P2Y12 receptor inhibitors before coronary anatomy is known (i.e., pretreatment) remains a matter of debate [5–7]. In the ACCOAST trial (A Comparison of Prasugrel at PCI or Time of Diagnosis of Non-ST Elevation Myocardial Infarction) [8], 4033 NSTEMI patients were randomly assigned to receive prasugrel as pretreatment (2 to 48 h before coronary angiography) or to receive prasugrel after angiography, if PCI was planned. Pretreatment with prasugrel did not reduce the 30-day rate of major ischemic events and produced an increase of major or life-threatening bleeding events. Consistently with the observed harm associated to this strategy, current guidelines do not recommend pretreatment with prasugrel in NSTE-ACS (class III, level of evidence B) [1]. To date, there are no head-to-head comparisons between upstream and downstream administration of ticagrelor in NSTE-ACS patients [3]. However, in the PLATO study (A Comparison of Ticagrelor [AZD6140] and Clopidogrel in Patients With Acute Coronary Syndrome) [2], pretreatment with the assigned P2Y12 inhibitor was mandatory per-protocol, and ticagrelor was associated with an early benefit over clopidogrel in invasively managed NSTE-ACS patients irrespective of the timing of angiography [9]. Based on such observations, the European Society of Cardiology (ESC) guidelines have provided divergent recommendations over the years, although most recent guidelines recommend that with class IIa, level of evidence C, pretreatment with ticagrelor be considered as soon as the diagnosis is established [3]. On the contrary, the American College of Cardiology/American Heart Association (ACC/AHA) guidelines are essentially silent on the optimal timing of P2Y12 inhibitor administration and refer to the how the drugs were tested in their pivotal trials [10]. As far as choice of P2Y12 receptor inhibitors in NSTE-ACS patients, both prasugrel and ticagrelor are preferred over clopidogrel when no contraindications are present [3]. Nevertheless, there are no head-to-head comparisons of ticagrelor versus prasugrel specifically in the setting of NSTE-ACS. Recently, 4018 patients with acute coronary syndromes were enrolled in the ISAR-REACT-5 trial (Intracoronary Stenting and Antithrombotic Regimen: Rapid Early Action for Coronary Treatment) and randomized to receive ticagrelor or prasugrel [11]. This trial showed a lower incidence of death, myocardial infarction, or stroke among those who received prasugrel than among those who received ticagrelor, with similar incidence of major bleedings between arms. However, this trial enrolled a mixed population comprising both patients with ST elevated myocardial Infarction and NSTE-ACS. To note, in the subgroup of patients with NSTE-ACS, ticagrelor was to be administered always before angiography, while pretreatment with prasugrel was not allowed. Accordingly, the ISAR-REACT-5 was designed as a comparison of a ticagrelor-based strategy versus a prasugrel-based strategy rather than merely a head-to-head comparison of agents [11]. Currently, guidelines do not provide any specific recommendation in favor of ticagrelor (either upstream or downstream) over prasugrel [1].

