
Based on such gaps in the evidence, the DUBIUS (Downstream versus Upstream strategy for the administration of P2Y12 receptor Blockers In non-ST elevated acUte coronary Syndromes with initial invasive indication) study was conceived. The primary objectives of this clinical study are (1) to evaluate the impact of a pretreatment strategy based on ticagrelor administration compared to a no pretreatment strategy based on the downstream administration of ticagrelor or prasugrel in a population of NSTE-ACS patients with an indication to undergo invasive evaluation (coronary angiography planned within 72 h from admission) and (2) to evaluate the impact of downstream ticagrelor compared to downstream prasugrel in patients treated by PCI. Study groups will be compared by means of a combined measure of efficacy and safety endpoints (net clinical benefit). In particular, net adverse cardiac events (NACE) will be assessed at 30 days and 12 months. In this paper, we report the study protocol of the DUBIUS study in accordance with the Standard Protocol Items: Recommendations for Clinical Interventional Trials (SPIRIT) guidelines (Additional file 1).

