The primary powered hypotheses include (1) superiority of a downstream administration strategy for P2Y12 receptor blockers over the upstream administration and (2) non-inferiority of prasugrel versus ticagrelor in the PCI group of the downstream strategy arm. The study is powered based on the primary endpoint of incidence at 30 days of the combined primary endpoint. For the comparison of upstream and downstream arms, the intent-to-treat (ITT) population will be considered. The study will provide 80% power to establish the superiority of the downstream strategy on the upstream strategy relative to the primary composite endpoint. These calculations are based on the following assumptions: (1) 8% of patients in downstream arm and 11% of patients in the upstream arm (odds ratio = 1.4) having a primary endpoint event within 30 days from randomization, based on extrapolations of previous data. In particular, in patients with NSTE-ACS pretreated with ticagrelor, the 30-day incidence of a composite efficacy endpoint (comprising cardiovascular death, MI, stroke, TIA, or other arterial thrombotic event) was 6.95%, while the rate of major bleeding was 4.05% [19]. In patients with NSTE-ACS not pretreated with a P2Y12 inhibitor, the observed incidence of the composite efficacy endpoint at 30 days (cardiovascular death, MI, stroke) was 7.2%, while the incidence of non-CABG-related TIMI major bleeds was 0.6% and the incidence of all TIMI major bleeds (CABG-related or non-CABG-related) was 1.5% [8]; (2) the time-to-first event analysis based on a 2-sided log-rank test used at a 2-sided significance level (α) of .05 to assess superiority; (3) a dropout rate of about 10%.

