As a second target, non-inferiority of prasugrel versus ticagrelor in the PCI group of the downstream strategy will be considered. Analyses will be performed at the study completion, so no ad interim evaluations are assumed for this study group. Assuming that at least 80% of the patients will have an indication for PCI in the downstream group, based on the above calculations, a sample of about 1000 should be available for randomization in this group. The following assumptions were considered: (i) two-sided non-inferiority test for rejecting the hypothesis that prasugrel and ticagrelor will differ for more than 4% in terms of NACE, (ii) an overall confidence bounds in non-inferiority testing at 0.95 level (α = 0.025), (iii) an overall sample size of 1000 patients (500 prasugrel + 500 ticagrelor), and (iv) an anticipated incidence rate of 5% in downstream ticagrelor and 8.5% in downstream prasugrel and a true difference in incidence rates of 1% between treatment groups [1, 2, 8]. This approach combines the target clinically relevant maximal difference between treatments of 1% with previous information on a relevant distance in terms of effects between treatments (8.5% versus 5%) [21]. This design corresponds to the Palesch and Tilley “futility design” [22, 23], aimed at screening out-of-target therapeutic approaches, in particular in the cardiovascular field [23]. Power calculations have been made using the R-system [24] and gsDesign libraries [25]. For time-to-event variables, survival curves will be constructed using Kaplan-Meier estimates, and log-rank test results will be displayed for descriptive purposes only. Demographics, procedural, imaging, laboratory, exercise testing, quality of life, and diary related data that are not part of the list of endpoints will be displayed for descriptive purposes only.

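### The event rates behind the two primary sample-size calculations are not coherent, and the stated 80% power for the first hypothesis does not follow from its own inputs

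*Protocol article*

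**What the plan says.** All planning rates are in the Protocol article under Primary and secondary endpoints.

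- **First hypothesis (downstream superior to upstream, ITT population).** The 30-day NACE assumption is "8% of patients in downstream arm and 11% of patients in the upstream arm", with an odds ratio of 1.4, a "2-sided log-rank test used at a 2-sided significance level" of 0.05 and about 10% dropout. The claim is: "The study will provide 80% power to establish the superiority of the downstream strategy on the upstream strategy". The Abstract gives the total as 2520, randomised 1:1.
- **Second hypothesis (prasugrel non-inferior to ticagrelor, downstream PCI patients).** The group size rests on this: "Assuming that at least 80% of the patients will have an indication for PCI in the downstream group". That yields about 1000 patients, 500 per drug. The margin is 4% and α is 0.025. The planning rates are "an anticipated incidence rate of 5% in downstream ticagrelor and 8.5% in downstream prasugrel", followed by a true difference of 1%. No power is stated.

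The article gives no rate for downstream patients who do not have PCI, and none for events between admission and the second randomisation. It does not say how 8% relates to 5% and 8.5%.

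**The concern.** Both hypotheses are called primary and powered, and the second uses a subset of the patients in the first. The two sets of rates should therefore fit together, and each should support the size chosen. Three things do not fit:

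1. Within the second calculation, 5% and 8.5% differ by 3.5 points, yet the true difference is given as 1 point. With a 4-point margin the choice between them decides whether the comparison has any useful power.
2. Across the two calculations, the PCI rates pool to well below the 8% assumed for the arm that those patients mostly make up. The article offers no bridge.
3. Within the first calculation, the stated power is not what the stated inputs give at the stated size.

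At stake is how a reader should judge an inconclusive result on either hypothesis. The article suggests adequate power for both, and its own figures do not bear that out.

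**Working it through.** **1. First hypothesis: the stated 80%.**

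Inputs: 8% and 11%, two-sided 0.05, 10% dropout (Primary and secondary endpoints); N = 2520 (Abstract), so 1260 per arm, or 1260 × 0.9 = 1134 after dropout. Odds ratio: (0.11/0.89)/(0.08/0.92) = 1.42, which agrees with the stated 1.4.

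Power = Φ[(0.03 − 1.96 × SE0)/SE1], where SE0 = √(2 × 0.095 × 0.905/n) and SE1 = √((0.08 × 0.92 + 0.11 × 0.89)/n).

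- n = 1134: SE0 = 0.01231, SE1 = 0.01230, z = 0.477, power **68%**.
- n = 1260: SE0 = 0.01168, SE1 = 0.01167, z = 0.609, power **73%**.

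The same formula solved for 80% power needs 1499 per arm, 2998 in total, or 2998/0.9 ≈ 3332 with dropout. Log-rank event formulas (Schoenfeld, Freedman) give about 2958 to 3011 before dropout, so the choice of test does not explain the gap. A one-sided 0.05 test comes close (79% at 1134 per arm, 82% at 1260), but the article says two-sided. Three looks with equally spaced stages (an assumption) do not help: about 68% at 1134 per arm with O'Brien-Fleming boundaries and 61% with Pocock.

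**2. Second hypothesis: 5% and 8.5% against a 1% difference.**

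Inputs: margin 0.04, 500 per group, one-sided 0.025, all from the same section. Prasugrel is tested against ticagrelor, as that section states.

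Power = Φ[(0.04 − (pP − pT))/SE − 1.96], with SE = √(pT(1 − pT)/500 + pP(1 − pP)/500).

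| Ticagrelor | Prasugrel | SE | Power |
|---|---|---|---|
| 5% | 8.5% | 0.01583 | 5% |
| 5% | 6% | 0.01442 | 55% |
| 7.5% | 8.5% | 0.01716 | 42% |
| 5% | 5% | 0.01378 | 83% |

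The first row uses the stated rates. The second and third keep one stated rate and apply the stated 1-point difference; the article names neither pair. Only the last row, with no difference at all, passes 80%, and it matches neither stated assumption. The Abstract words the hypothesis the other way round (ticagrelor non-inferior to prasugrel). At 5% v 8.5% that direction would have about 99.7% power, so these figures hold for the direction in the Methods.

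**3. Do the PCI rates fit the 8% arm rate?**

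The second randomisation is 1:1 (Consenting and randomization), so the pooled PCI rate is (5 + 8.5)/2 = 6.75%. If a share f of the arm has PCI and the rest has rate r, the arm rate is f × 6.75 + (1 − f) × r. Setting this to 8%:

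- f = 0.80: r = (8 − 5.4)/0.20 = **13.0%**
- f = 0.85: r = (8 − 5.7375)/0.15 = 15.1%
- f = 0.90: r = (8 − 6.075)/0.10 = 19.3%

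The article says at least 80%, so 13% is the lowest of these. It assumes that no events fall before the second randomisation. If x% of the arm has such an event (x is an assumption), the break-even at f = 0.80 is about (8 − x − 5.4)/0.2: 10.5% at x = 0.5 and 8% at x = 1.

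**The case against.** **Different populations and clocks.** The 8% covers the whole ITT arm and counts events from the first randomisation, soon after admission. The 5% and 8.5% cover only PCI patients, who are randomised again after angiography, and angiography may come up to 72 h after admission. Table 3 even lists NACE between admission and revascularisation as an endpoint of its own. Non-PCI patients include those sent to CABG, and CABG-related bleeding (BARC type 4) counts in NACE, so a higher rate in that group has a reason behind it. This stands. A reader might infer that no set of downstream rates can satisfy both calculations; the documents do not support that. Nor can one speak of two stated powers, because the second calculation states none. What remains is that the reconciling figures are not given.

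**The 1% and the 3.5 points play different roles.** The article presents 1% as the target difference and 8.5% v 5% as earlier information on the distance between the drugs, within a futility-type design. That may explain why both appear. But the sentence lists both as planning assumptions, fixes no pair of rates 1 point apart, and reports no power for any reading.

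**Sample size reassessment.** The first hypothesis has three stages with reassessment on observed NACE rates, so the final size may exceed 2520. That could restore power. The 80% is, however, attributed to the listed assumptions and not to a later increase. The second hypothesis has no interim evaluation.

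**Direction of any bias.** If the PCI rates are right, the arm rate may be below 8% and the first comparison has more power, so 8% is the cautious choice. This stands. A reader might also infer that part of the no-pretreatment benefit would really be ticagrelor's assumed advantage over prasugrel. That is backwards: the upstream arm receives only ticagrelor, so a prasugrel share downstream would dilute the benefit.

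**Conclusion.** The point holds as an incoherence in the planning figures, in three parts.

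- **Second hypothesis, internal conflict (firm).** A 3.5-point gap and a 1-point true difference cannot both be the design assumption. Power for prasugrel non-inferiority is about 5% on the stated rates and 42% to 55% with a 1-point difference. This assumes a normal approximation, 500 evaluable patients per group and the direction given in the Methods.
- **First hypothesis, power (firm).** The stated inputs give about 68%, or 73% with no dropout, against a claimed 80%. This does not depend on the second set of rates.
- **Between the two (unexplained, not impossible).** The rates agree only with a non-PCI rate of about 13% or more, or with some events before the second randomisation. Neither is stated. The 13% rests on an 80% PCI share, a 1:1 split and no early events.

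The correction is cheap and concerns figures on which the trial's claims to power rest, so it should be made.

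**What to change.** In the sample-size text of Primary and secondary endpoints:

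1. State one set of downstream 30-day NACE rates: ticagrelor PCI, prasugrel PCI, non-PCI, and any events before the second randomisation, with the PCI share. Show how they combine into the whole-arm rate.
2. Remove the conflict between 5%/8.5% and the 1% difference by naming the pair of rates at which the non-inferiority test is evaluated.
3. Restate the power achieved for both hypotheses at the planned sizes (2520 in total, 500 per drug), with dropout applied. If the 80% relies on reassessment, say so.

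The 8% should not be swapped for a lower mixture rate merely to raise the apparent power. At an assumed non-PCI rate of 8% to 11%, the mixture would be 0.8 × 6.75 + 0.2 × 8 = 7.0% to 0.8 × 6.75 + 0.2 × 11 = 7.6%. Power would then read 91% to 80% at 1134 per arm on the strength of an unsupported figure. The stage-wise reassessment should stay on observed rates.

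The cost is recalculation and rewording, with no new procedures and no extra patients for the correction itself. The downside is that the stated power becomes less favourable.

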
### Outcome measures

The primary outcome measure (NACE, net adverse cardiac events) is a composite of death from vascular causes (death from cardiovascular causes or cerebrovascular causes and any death without another known cause), non-fatal MI, or non-fatal ischemic stroke, and BARC type 3, 4, and 5 bleeding. The rationale for choosing this composite endpoint was to use a balanced estimate of the effect regarding irreversible organ damage, that is, MI, stroke, plus an estimate of life-threatening and fatal bleedings. Cardiovascular death includes death with a demonstrable CV cause, or any death that is not clearly attributable to a non-CV cause. To be considered a primary endpoint event, an MI must be distinct from the index event. Definitions of spontaneous, PCI-related, and CABG-related MI will be adjudicated based on the third universal definition of myocardial infarction [15]. Stroke is defined as a rapid onset of a new persistent, neurological deficit that lasts for more than 24 h (excluding hemorrhagic stroke). Bleeding includes major, life-threatening, or fatal events according to BARC type 3, 4, and 5 definitions (Table 2). Secondary outcome measures include death from any cause and stent thrombosis. Stent thrombosis is based on Academic Research Consortium definitions and comprises angiographic or pathological confirmation, as well as clinical determination of stent thrombosis [16]. Secondary safety endpoints include BARC type 2, 3, 4, and 5 bleeding; any TIMI major, life-threatening, and minor bleeding; CABG surgery-related TIMI major and minor bleeding; and non-CABG surgery-related TIMI major and minor bleeding [17, 18].

**Table 2 Tab2:** Type 3–5 bleeding criteria according to the BARC classification

Type 3	
Type 3a	
Overt bleeding plus hemoglobin drop of 3 to < 5 g/dL (provided hemoglobin drop is related to bleed)	
Any transfusion with overt bleeding	
Type 3b	
Overt bleeding plus hemoglobin drop ≥ 5 g/dL (provided hemoglobin drop is related to bleed)	
Cardiac tamponade	
Bleeding requiring surgical intervention for control (excluding dental/nasal/skin/hemorrhoid)	
Bleeding requiring intravenous vasoactive agents	
Type 3c	
Intracranial hemorrhage (does not include microbleeds or hemorrhagic transformation, does include intraspinal)	
Subcategories confirmed by autopsy or imaging or lumbar puncture	
Intraocular bleed compromising vision	
Type 4: CABG-related bleeding	
Perioperative intracranial bleeding within 48 h	

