### Primary and secondary endpoints

The primary hypothesis will be tested comparing study groups in terms of the 30-day incidence of the combined efficacy and safety primary endpoint (NACE). A list of safety and efficacy endpoints is reported in Table 3.

**Table 3 Tab3:** Secondary endpoints

Single digit and composite of death from vascular causes (death from cardiovascular causes or cerebrovascular causes and any death without another known cause), MI, stroke, TIA, severe recurrent ischemia, recurrent ischemia, or other arterial thrombotic event	
Death from any cause	
Any stent thrombosis according to the ARC criteria	
Target vessel revascularization (TVR)	
Target lesion revascularization (TLR)	
NACE (net adverse cardiac events) occurred in the period between admission and coronary revascularization defined as a composite of death from vascular causes (death from cardiovascular causes or cerebrovascular causes and any death without another known cause), non-fatal MI, or non-fatal stroke, and BARC type 2, 3, 4, and 5 bleeding	
Compliance to mandated antiplatelet therapy	
BARC type 2, 3, 4, and 5 bleeding (single digit and composite)	
All TIMI major, major life-threatening, and minor bleeding	
All CABG surgery-related TIMI major, minor, and composite of TIMI major or minor bleeding	
Non-CABG surgery-related TIMI major, minor, and composite of TIMI major or minor bleeding	

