### Clinical follow-up and assessment of outcomes

The assessment of clinical endpoints and adverse events will take place during hospital stay, at hospital discharge, at 30 ± 7 days (office visit), and at 12 months ± 30 days (office visit) (Fig. 2). Data collection forms are available in the e-CRF at https://redcap.dctv.unipd.it. e-CRF printout is reported in Additional file 3. Investigators at each eligible site will be preliminarily trained by the coordinating center in order to promote data quality related to both clinical data and clinical events. Clinical documentation of each patient experiencing adverse events will be kept at the enrolling sites and made available for the clinical events committee. Investigators at each site will be trained to collect and report any additional reported adverse events and unintended effects of trial interventions or trial conduct by inclusion in the e-CRF or telephone/e-mail contact with the coordinating center, as appropriate. Outcome data of participants who discontinue or deviate from intervention protocols will be collected in a similar manner to those with a satisfactory adherence to study protocol. The responsible person for pharmacovigilance will be available 24/24 h 7/7 days at [contact] and [contact], [contact], [contact], and [contact]. Data collection forms will be available in the e-CRF at https://redcap.dctv.unipd.it. The e-CRF printout is available in the Trial Master File and in each center in the appropriate section of Investigator’s Site File.

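### Kaplan-Meier is the only estimator named for time-to-event variables; for single endpoints that death precludes, an incidence read from it would be slightly too high

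*Protocol article*

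**What the plan says.** At the end of the power discussion under Primary and secondary endpoints, the protocol article states: "For time-to-event variables, survival curves will be constructed using Kaplan-Meier estimates". The sentence continues: "and log-rank test results will be displayed for descriptive purposes only". It makes no exception by endpoint, and the article names no competing-risk estimator.

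Table 3 in the same section lists the secondary endpoints. Several are to be reported singly as well as in composites: vascular death, MI, stroke, TIA and recurrent ischaemia, and each BARC bleeding type. Others stand alone, for example "Any stent thrombosis according to the ARC criteria", target vessel revascularization and target lesion revascularization. Death from any cause is a separate entry. The table gives no time points.

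The primary composite, NACE, is defined under Outcome measures as "death from vascular causes (death from cardiovascular causes or cerebrovascular causes and any death without another known cause), non-fatal MI, or non-fatal ischemic stroke" together with BARC type 3, 4 and 5 bleeding. The Introduction says that "net adverse cardiac events (NACE) will be assessed at 30 days and 12 months", and the follow-up schedule has a last office visit at 12 months. The powered comparison is at 30 days: "The study is powered based on the primary endpoint of incidence at 30 days of the combined primary endpoint".

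**The concern.** Kaplan-Meier assumes that a censored patient could still have the event later, at the same rate as those who remain under observation. That is reasonable for a patient lost to follow-up. It is not reasonable for a patient who has died: a dead patient cannot have a stent thrombosis or a repeat revascularization. When such deaths are censored, one minus Kaplan-Meier estimates the risk in a hypothetical population in which nobody dies, and that risk is higher than the proportion of randomised patients who have the event.

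Two things would be at stake. Displayed 12-month incidences of single endpoints would be a little too high. The inflation would also be larger in the arm with more deaths, so part of a mortality difference could appear as a difference in MI, stent thrombosis or bleeding.

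**Working it through.** **No figure to reproduce.** The article gives no 12-month component incidence and no 12-month mortality. The inputs below are therefore assumptions, shown over a range.

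**Which deaths compete**
- Single endpoints that death precludes (MI, stroke, TIA, recurrent ischaemia, stent thrombosis, TVR, TLR, non-fatal bleeding types): deaths that occur before the event.
- NACE and the vascular-death composites: only deaths with a known non-vascular cause, because vascular deaths and deaths without another known cause are events.
- Bleeding composites that include BARC type 5: only deaths not due to bleeding.
- Death from any cause: none, so Kaplan-Meier is right there.

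**Formula.** Let I be the true 12-month incidence of the endpoint and D the 12-month proportion dying without it, with constant cause-specific hazards.
- Total cumulative hazard: H = -ln(1 - I - D)
- The endpoint's share: H × I/(I + D)
- One minus Kaplan-Meier with death censored: 1 - exp(-H × I/(I + D))
- Excess: that value minus I

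**Example.** With I = 10% and D = 8%:
- H = -ln(0.82) = 0.1985
- 0.1985 × 10/18 = 0.1103
- 1 - exp(-0.1103) = 10.44%, an excess of 0.44 points

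With I = 6% and D = 8%, H = -ln(0.86) = 0.1508, the endpoint's share is 0.0646, and the result is 6.26%.

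**Excess in percentage points over the assumed range**

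| D | I = 1% | I = 3% | I = 5% | I = 8% | I = 10% |
|---|---|---|---|---|---|
| 1% | 0.005 | 0.015 | 0.026 | 0.041 | 0.052 |
| 2% | 0.010 | 0.031 | 0.052 | 0.083 | 0.105 |
| 3% | 0.015 | 0.046 | 0.078 | 0.126 | 0.159 |
| 5% | 0.026 | 0.078 | 0.132 | 0.213 | 0.268 |
| 8% | 0.042 | 0.128 | 0.215 | 0.348 | 0.439 |

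The relative excess depends almost only on D: about 0.5% at D = 1%, 1.5% at 3%, 2.6% at 5% and 4.2-4.4% at 8%.

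**Upper bound.** If every death came before any event, one minus Kaplan-Meier would equal I/(1 - D). For I = 10% and D = 8% that is 10.87%, an excess of 0.87 points. This is an extreme case, not an expectation.

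**Spill-over between arms.** With the same true incidence of 10% in both arms and deaths of 3% and 8%, the curves would show 10.16% and 10.44%, a spurious difference of 0.28 points.

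**NACE.** With an assumed 12-month incidence of 15% and non-vascular death of 0.2-2%, the excess is 0.016-0.16 points. At 30 days, with the planned upstream rate of 11% and non-vascular death of 0.02-0.2% (assumed), it is 0.001-0.011 points.

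**The case against.** The strongest reply is that the error is inferred. The article states no censoring rule, does not say which Table 3 endpoints are treated as time-to-event variables, and does not say that incidences will be read from the curves. Its 12-month statement concerns NACE, not stent thrombosis or revascularization. A condensed article may leave the handling of death to the full protocol or SAP, and the curves are secondary displays.

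Much of this stands. A reader might infer that the plan fixes death as censoring and that every 12-month incidence of a non-fatal endpoint will be overstated. The text does not go that far, so the point is conditional: it applies if death is censored and one minus Kaplan-Meier is shown as incidence. It also does not apply equally to all endpoints, because NACE, the vascular-death composites and the bleeding composites already count some deaths as events.

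What does not stand is that there is nothing to correct. The estimator is stated without exception, and censoring at death is its ordinary use for a single non-fatal endpoint; any other handling would need a rule that the article does not give. The descriptive status of the displays removes the inferential stakes, but a displayed curve is still read as the incidence in that arm.

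The objection on size is also fair. With about 1,260 patients per arm (2520/2), the standard error of a difference between two rates of 10% is √(2 × 0.10 × 0.90/1260) = 1.2 points. The spurious 0.28 points is about a quarter of that, and it requires a five-point mortality gap. Such a gap would be about 5.5 standard errors (0.05/√((0.03 × 0.97 + 0.08 × 0.92)/1260) = 0.05/0.0090) and would be a major result in itself, visible in the separate report of death from any cause.

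**Conclusion.** The point holds as a minor one. Kaplan-Meier is the only estimator named and is not the best choice for single endpoints that death precludes. In its ordinary use, any 12-month incidence read from it would be too high by about 0.005-0.44 percentage points, roughly 0.5-4% in relative terms. This rests on assumed incidence of 1-10%, assumed competing mortality of 1-8% and constant hazards, none of which comes from the article. The direction is certain once death is censored and some deaths precede the event; the size is not.

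It would be wrong to conclude that the trial's main results are at risk. The 30-day primary endpoint counts most deaths as events, few competing deaths can occur in 30 days, and a log-rank test remains valid as a comparison of cause-specific hazards. No confirmatory conclusion changes.

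**What to change.** In the sentence on time-to-event variables under Primary and secondary endpoints:

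- Keep Kaplan-Meier for death from any cause. No composite listed in the article includes all deaths, so it is the only listed endpoint for which no death competes.
- For time-to-event endpoints that leave out some or all deaths, display Aalen-Johansen cumulative incidence by arm with confidence intervals. Treat the deaths that the endpoint does not count as the competing event: for example, non-vascular death for NACE and the vascular-death composites, and death without the event for stent thrombosis or revascularization.
- Keep the descriptive log-rank tests, labelled as cause-specific comparisons.

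The cost is one sentence and a few lines of code. No new data are needed, since death and its cause are already collected for the endpoints. The only visible effect is slightly lower displayed incidences. The article's section on deviations from the statistical plan already provides a way to document the change.
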